### Subgroup analyses

4.11

Exploratory subgroup analyses will be conducted to examine whether treatment effects vary across key demographic and clinical characteristics. Subgroups will include age categories (45–50 vs. 51–55 years), BMI classifications (normal vs. overweight), and baseline insomnia severity (sub-threshold vs. moderate insomnia based on ISI scores). In addition, Ayurvedic baseline assessments—including *Prakriti* (individual body constitution) profiling and documentation of *Dosha dushti lakshana (symptoms associated)* associated with *Nidranasa*—will be incorporated to explore potential correlations between *Dosha* predominance and insomnia severity. These analyses are exploratory in nature and intended to generate hypotheses for future confirmatory studies. All statistical analyses will be performed using R version (4.1.5).

### Interim analysis

4.12

Interim analysis is not planned for this study. The intervention is a non- pharmacological behavioral therapy (Cognitive Behavioral Therapy for Insomnia) posing minimal risk to participants. The study duration and sample size are such that interim analysis is not required. All analyses will be conducted after the completion of data collection.

### Auditing

4.13

Being a minimally risk posing intervention, a formal independent audit is not planned. Trial is conducted entirely within a clinical setting with routine monitoring of trial conduct and data quality by the Principal Investigator (PI) and the study team through regular team meetings and review of source documents, case report forms, and consent forms. The Institutional Ethics Committee (IEC) may perform audits or monitoring visits at its discretion to ensure compliance with the approved protocol, ethical standards, and applicable regulations. Although any audit requests from the IEC will be fully facilitated by the study team.

### Safety

4.14

All adverse events (AEs) and serious adverse events (SAEs) will be systematically documented in the Case Report Form (CRF) using a predefined Adverse Drug Reaction (ADR) page. Each entry will capture the event description, diagnosis (if available), onset and resolution dates, severity (mild, moderate, or severe), action taken with the study drug (none, temporarily interrupted, or permanently withdrawn), outcome (resolved, resolved with sequelae, or not resolved), and the assessed relationship to the study drug (definite, probable, possible, unlikely, not related, or not assessable). The Principal Investigator and Co-Investigator will independently evaluate causality, taking into account the temporal relationship with the study drug, the participant’s clinical course, medical history, and concomitant medications. All adverse events will be actively managed by the study investigators with access to on-site medical services at the study institution. Escalation will follow institutional clinical pathways, including specialist referral when indicated. Costs of medical management for trial-related adverse events will be borne by the institution in accordance with ethical guidelines.

Events occurring after a participant exits the study will not be routinely reported unless the investigators consider a reasonable likelihood of relation to the study drug, psychotherapy, or study procedures. This systematic documentation ensures continuous monitoring and prioritization of participant safety throughout the trial.

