#### Cognitive Behavioral Therapy for Insomnia (intervention and control group)

3.6.3

Participants randomized to the control arm will receive Cognitive Behavioral Therapy for Insomnia (CBT-I) alone for 4 weeks. CBT-I will be delivered twice weekly in 45–60-min individual sessions, either in person or via telehealth, by trained and certified counseling psychologists with a minimum of 2 years of clinical experience. All CBT-I therapists will undergo a protocol orientation meeting prior to study initiation to ensure adherence to the standardized CBT-I manual used in this trial. Session content will be documented after each visit using structured therapist notes. Treatment will follow the same standardized CBT-I manual as described, including sleep restriction therapy, stimulus control therapy, cognitive restructuring, sleep hygiene education, and relapse prevention components.

Participants in the control arm will undergo the same follow-up schedule, outcome assessments, adherence monitoring procedures, and safety oversight as those in the intervention arm to ensure methodological parity between groups. A sham oleation procedure was not included, as standardizing a credible placebo tactile intervention was considered impractical in the context of this exploratory trial.

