#### Mild to moderate symptoms

3.10.1

*Dhanwantharam Gulika* for mild headache.Steam inhalation and *Vyoshadi Vatakam* for nasal congestion.*Jeerakarishtam* for light-headedness.Coconut oil for mild local skin irritation.Warm water and light ambulation for drowsiness.Short nap (<30 min), sunlight exposure for daytime sleepiness.Breathing exercises and progressive muscle relaxation for irritability and stress.Motivational guidance for schedule adjustment difficulties.

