### Exploratory secondary outcomes

4.2

The following outcomes explore early response, durability of effect, sleep quality, safety, behavioral reliance, and adherence. These analyses are exploratory and descriptive in nature. No adjustment for multiple comparisons is planned.

Pittsburgh Sleep Quality Index (PSQI) — change from baseline to Week 4.

Measurement variable: PSQI global score (range 0–21).Analysis metric: Mean change from baseline to Week 4; between-group mean difference with 95% confidence interval.

Early therapeutic response (ISI at Week 2).

Measurement variable: ISI total score at Week 2.Analysis metric: Between-group differences in mean change from baseline with 95% confidence intervals.

Durability of insomnia severity (ISI during follow-up).

Measurement variable: ISI total scores at Weeks 6, 8, 10, 12, 14, 16.Analysis metric: Mean change from baseline at each time point; descriptive summaries with between-group estimates.

Sleep quality during follow-up (PSQI).

Measurement variable: PSQI global scores at Weeks 8, 12, 16.Analysis metric: Mean change from baseline; descriptive between-group estimates.

Occurrence and characterization of clinically relevant events.

Measurement variable: Adverse events recorded using validated ADR/AE monitoring checklist (45, 46).Analysis metric: Frequency and proportion by group; descriptive summaries of severity and relatedness.

Behavioral dependency risk.

Measurement variable: Severity of Dependence Scale (SDS) total score (47), assessed through Week 16.Analysis metric: Mean change from baseline to Week 16; between-group estimates with 95% confidence intervals.

Treatment adherence and fidelity.

Measurement variable: Daily Sleep and Treatment Engagement Diary (DSTED) (48).Analysis metric: Percentage adherence and descriptive summaries.

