#### Documentation

4.4.2

All AEs will be documented in standardized Case Report Forms including:

Event description.Date of onset and resolution.Severity of the event (mild, moderate, severe).Assessed relatedness to study intervention.Action taken.Outcome.

The Principal Investigator will be evaluating each event for severity and causality.

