#### Serious adverse events

4.4.3

Any SAE will be reported to the Institutional Ethics Committee (IEC) within 24 h of awareness Appropriate clinical evaluation, referral and management will be initiated immediately.

In cases where an AE is considered probably or definitely related to the intervention and is of moderate or severe intensity, the intervention will be discontinued for that participant and standard care will be provided. Participants can report issues using emergency contact details provided in the informed consent.

All rescue medications and supportive measures will be documented for outcome interpretation. Due to low risk nature of the trial interventions, no interim harm-related analysis is planned, but continuous safety oversight will be maintained. Participants will be advised to promptly report any discomfort, worsening of insomnia symptoms, headaches, skin irritation, allergic reactions to oils, slips/falls after the intervention or other unexpected physical/ psychological reactions.

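### Section 4.14 ties adverse-event causality, action and timing to a study drug, so CBT-I-related events have no clear code, in conflict with sections 3.6.3, 4.4.2 and 4.4.3

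*Protocol article*

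**What the plan says.** Section 4.14 (Safety) sends every adverse event and serious adverse event to a predefined adverse drug reaction page of the CRF. Two of its fields name the drug: "action taken with the study drug (none, temporarily interrupted, or permanently withdrawn" and "the assessed relationship to the study drug (definite, probable, possible, unlikely, not related, or not assessable". The two evaluators are also told to weigh timing relative to the study drug. The closing paragraph of the section, on events after a participant leaves the study, is wider and refers to "a reasonable likelihood of relation to the study drug, psychotherapy, or study procedures".

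Other sections use different terms:
- Section 4.4.2 (Documentation) lists the CRF content for all adverse events, including "Assessed relatedness to study intervention" and an action field with no restriction.
- Section 4.4.3 sets the stop rule: "In cases where an AE is considered probably or definitely related to the intervention and is of moderate or severe intensity", the intervention is discontinued for that participant and standard care is given.
- Section 3.6.3 gives control women CBT-I alone and promises them the same follow-up, assessments, adherence monitoring "and safety oversight as those in the intervention arm to ensure methodological parity between groups".
- Section 4.2 lists the safety metric as "Frequency and proportion by group; descriptive summaries of severity and relatedness".

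**The concern.** The oil procedures are the only part of the regimen that could be called a drug, and only the add-on arm receives them. On the wording of 4.14, a control woman has no drug to which an event could be related and none that could be interrupted or withdrawn.

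The protocol expects CBT-I to cause some events. Section 8.2 names emotional distress during CBT-I as a possible risk. Section 3.10.1 plans for daytime sleepiness, irritability and stress, and offers "Motivational guidance for schedule adjustment difficulties". Sleep restriction is part of the CBT-I manual (3.6.3 and 3.6.3.1).

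Safety is a declared purpose of the trial, and relatedness is part of the listed safety outcome. If attribution is recorded for the oil only, the relatedness summary cannot separate what the oil adds from what CBT-I does in both arms. Attribution that is not recorded at the time of the event is hard to reconstruct later.

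**Working it through.** The plan gives no figure on this point and no expected event rate, so the check compares sections.

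**1. Could *study drug* be shorthand for all study treatment?** Not safely. The post-exit sentence of 4.14 lists drug, psychotherapy and study procedures as three separate causes. Psychotherapy is therefore recognised as a cause for events after exit, while the causality field in the same section leaves it out.

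**2. The terms side by side.**

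| Section | Element | Refers to |
|---|---|---|
| 4.14 | Action, causality, timing | Study drug |
| 4.14, post-exit events | Possible cause | Drug, psychotherapy or procedures |
| 4.4.2 | Relatedness | Study intervention |
| 4.4.2 | Action taken | Unrestricted |
| 4.4.3 | Stop rule | The intervention |

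Sections 4.4.2 and 4.14 describe the same CRF record, and a form cannot follow both without a choice.

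**3. Does 4.4.2 settle it?** Only in part. It gives no causality grades. Section 4.4 names the WHO–UMC framework without listing grades. Section 4.14 is the only place that spells out the scale, and there it is attached to the drug. The stop rule needs a rating of probable or definite. The word *intervention* also shifts: section 4.12 applies it to CBT-I, section 4.7.1 uses intervention group for the add-on arm, and Table 1 ties the event checklist to the integrative intervention.

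**4. One event traced through both versions.** Take daytime sleepiness caused by sleep restriction.
- *Control arm.* Under 4.4.2 it can be rated as related. Under 4.14 the field does not apply, or reads as not related or not assessable.
- *Add-on arm.* Under 4.14 it is either not attributed to any treatment or attributed to the oil.

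The oil procedures run on Days 1–7 and 1–14 (3.6.2), and CBT-I runs for 4 weeks, or 28 days. Oil and CBT-I therefore overlap for 14/28 = 50% of the CBT-I period. Charging a CBT-I event to the oil is most plausible in that half. In the second half, timing argues against the oil and the attribution is more likely to be lost.

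**5. Reach.** CBT-I is given to all 62 women. It is the only study treatment for 31 of them (31/62 = 50%).

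**6. What is untouched.** Section 4.4 counts events whether or not they are related, and the planned Chi-square or Fisher comparison in 4.9.2 is on event frequency by group. A missing relatedness code does not remove an event from that count.

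**The case against.** The strongest reply is that 4.14 contains loose wording and the working rules lie elsewhere. Section 4.4.2 gives all adverse events, in both arms, a field for relatedness to the intervention and an open action field. The stop rule in 4.4.3 uses the same term, and 4.12 calls CBT-I the intervention. Other safeguards do not depend on the drug wording: withdrawal for a serious event or an emerging psychiatric condition (3.8), referral for persistent symptoms (3.10.2), and a pause with specialist referral when insomnia worsens markedly (3.10.3). The CRF is not shown and may already be right.

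Much of this stands, and it rules out two stronger readings that a reader might infer. The first is that control-arm and CBT-I events can never be coded as related, so that the stop rule fails for them. The documents do not support this, because 4.4.2 and 4.4.3 can be read to cover CBT-I in either arm. The second is that misattribution would make a harmless oil look harmful in a significance test. No test of related events is planned: 4.9.2 tests event frequency, and 4.2 gives relatedness as a descriptive summary only. That reading would also need an assumed event rate and every CBT-I event in the add-on arm charged to the oil, although the evaluators must weigh timing and clinical course.

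The reply does not remove the contradiction. Nothing says that 4.4.2 prevails over 4.14, and 4.14 is the more detailed text and the only one with the grading scale.

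**Conclusion.** The point holds as an inconsistency with practical consequences. Section 4.14 conflicts with 4.4.2 and 4.4.3 and with the parity promised in 3.6.3, and it leaves open how CBT-I-related events are rated and acted on. If the page follows 4.14, relatedness summaries are not comparable between arms, and CBT-I effects in the add-on arm may be lost or charged to the oil. That condition is the main assumption, since the form itself is not shown.

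The size cannot be given as a number of events. The ambiguity concerns attribution for a component that all 62 women receive. The sample size, the ISI analysis and the overall event comparison do not change. It should be fixed, because safety is a stated aim and the correction is small.

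**What to change.** 1. In section 4.14, replace *study drug* with *study intervention* in the action, causality and timing wording. Record relatedness and action taken separately for (a) CBT-I, in both arms, and (b) the Ayurvedic oil procedures, in the add-on arm, with a not-applicable entry for controls. Keep the existing categories for both.
2. In section 4.4.3, state that the component rated probably or definitely related is the one discontinued.

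Separate ratings for *Siro-pichu* and *Padabhyanga* are optional. They use the same oil and overlap on Days 1–7, so the two may be hard to tell apart in that week.

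The cost is one revised CRF page and a minor amendment approved by the ethics committee under section 8.1. No visits, participants or tests are added.

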### Withdrawal criteria

3.8

Participants may be withdrawn from the study under the following circumstances:

Occurrence of a serious adverse event requiring urgent medical intervention.Initiation of pharmacological treatment for insomnia during the study period.Emergence of a psychiatric condition requiring immediate clinical management.Voluntary withdrawal of consent.

Symptom fluctuation or worsening insomnia severity alone will not constitute automatic withdrawal. Participants experiencing worsening symptoms will undergo clinical evaluation and supportive management. Non-compliance with the intervention schedule will be documented but will not automatically result in withdrawal. All randomized participants will be included in the intention-to-treat analysis wherever feasible.

Withdrawal decisions due to safety concerns will be made by the Principal Investigator in consultation with the Co-Investigator and documented in the CRF.

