### Harms and adverse events monitoring

4.4

Harms will be defined as any untoward medical occurrence, whether or not causally related to the intervention, including adverse events (AEs), adverse reactions, serious adverse events (SAEs), and unexpected events. Adverse events will be systematically recorded using the WHO–UMC (World Health Organization–Uppsala Monitoring Center) causality assessment framework.

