#### Retention

4.8.4

Participation in this study is entirely voluntary. Participants may withdraw at any time without penalty or loss of entitled care and this will be documented in study records. Participants who withdraw will not undergo any additional data collection or follow-up assessments. Data collected prior to withdrawal will be retained for analysis unless the participant explicitly requests removal, subject to regulatory and ethical guidelines. Efforts will be undertaken, where appropriate and ethically permissible, to minimize unnecessary dropouts while respecting participant autonomy. All study records will be retained for a minimum of 5 years following study completion in accordance with institutional policy and Indian Council of Medical Research (ICMR) guidelines.

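### Safety data collection stops at withdrawal, even withdrawal for harm, so the later course of open events and late events up to Week 16 are captured only in part and selectively

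*Protocol article*

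**What the plan says.** All references are to the Protocol article.

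- **3.8 Withdrawal criteria.** The first ground on which a participant may be withdrawn from the study is "Occurrence of a serious adverse event requiring urgent medical intervention". Another is a psychiatric condition that emerges and needs immediate management.
- **4.8.4 Retention.** "Participants who withdraw will not undergo any additional data collection or follow-up assessments". No exception is made for an adverse event that is still open. On data already held: "Data collected prior to withdrawal will be retained for analysis unless the participant explicitly requests removal, subject to regulatory and ethical guidelines".
- **4.14 Safety.** "Events occurring after a participant exits the study will not be routinely reported", unless the investigators see a reasonable likelihood that the event is related to study treatment, psychotherapy or procedures.
- **4.4 Harms and adverse events monitoring.** "Harms will be defined as any untoward medical occurrence, whether or not causally related to the intervention".
- **4.4.2 Documentation.** The required fields include "Date of onset and resolution". Section 4.14 repeats this and adds an outcome field with three codes, none of which means unknown or lost to follow-up.
- **4.4.1.1, 4.4.1.2 and 4.4.3.** Adverse events are screened at every contact up to Week 4 and at each follow-up visit after that. Serious events go to the ethics committee within 24 hours.

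**The concern.** Safety is one of the trial's declared aims, and the event record is the evidence for it. Section 4.2 reports events by frequency and proportion in each group, with severity and relatedness. The plan observes women for events until Week 16, but that observation stops early for those who withdraw, and some of them withdraw because of harm.

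After exit, relatedness decides whether an event is recorded at all. That judgement belongs in the analysis of recorded events. Here it acts as a filter on recording, and it may be made by someone who knows the arm: the co-investigators who teach the Ayurvedic procedures are unblinded (4.7.3.2), and a co-investigator shares the causality assessment (4.14).

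**Working it through.** **1. Follow three kinds of event through the rules for a woman withdrawn under 3.8.**

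- *Event begins and ends before exit.* It is picked up by the contacts in 4.4.1, entered with all fields, and kept by default under 4.8.4. Nothing is lost.
- *Event begins before exit and is open at exit.* Its occurrence, severity and relatedness are recorded. Section 4.8.4 then ends data collection, so no planned contact supplies the resolution date or final outcome. It can be coded as not resolved at last contact, but that code then mixes events that truly persisted with events nobody followed.
- *Event begins after exit and before Week 16.* Section 4.14 lets it in only if judged reasonably likely to be related. Section 4.8.4 removes the contact through which investigators would learn of it, so it is recorded only if the woman volunteers it and it passes that judgement. Section 4.4 counts harms whatever their cause.

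The first kind is sound. The second is incomplete. The third is both incomplete and selective.

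**2. Observation time at stake.** *Siro-pichu* ends on Day 7 and *Padabhyanga* on Day 14 (3.6.2); follow-up ends at Week 16, which is 16 × 7 = 112 days. A woman withdrawn on Day 10 (an assumed date) loses 112 − 10 = 102 days, or 102/7 ≈ 14.6 weeks. Withdrawal at Week 4 loses 12 weeks, and at Week 8 it loses 8.

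**3. Number of women.** Section 4.5 inflates 26 per group for 15% attrition: 26/0.85 = 30.6, rounded up to 31 per arm and 62 in all, which reproduces the plan's figure. At that rate 0.15 × 62 = 9.3 women leave, or 0.15 × 31 = 4.65 per arm, for any reason. The documents give no rate of withdrawal for harm.

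**4. Effect on the reported proportion.**

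- *Unreported late event.* The woman stays in the denominator. If she had no earlier event, each such case lowers her arm's proportion by 1/31 = 3.2 percentage points. The ceiling at planned attrition is about 5/31 = 16.1 points. It would require every leaver in the arm to have a first event after exit and none to be reported, so it is a bound and not a forecast.
- *Record removed on request.* The woman leaves numerator and denominator together. Assume 5 of 31 women in an arm have an event (16.1%). With no requests the figure stays at 16.1%. Removing one, two or three of those records gives 4/30 = 13.3%, 3/29 = 10.3% or 2/28 = 7.1%.

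**The case against.** A reader might infer that the safety outcome loses the very events that made women leave. The documents do not support that. Such events occur before exit, are entered in the case report form and are retained by default, and serious ones also reach the ethics committee.

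A reader might also infer that a withdrawing woman can have her event record erased at will. Removal needs an explicit request and is limited by regulatory and ethical guidelines. Adverse event data are not exempted, but nothing suggests that requests will be common. Nor is it right that the form cannot be completed: a code for unresolved events exists, and the frequency, severity and relatedness summaries in 4.2 need no resolution date.

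Three further points on the other side are fair.

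- Section 4.8.4 opens with voluntary withdrawal and may be meant only for women who choose to leave. Its sentence on further data collection is not limited to them, however, and no other section provides data follow-up for women withdrawn by the investigator.
- Not every harm leads to study exit. Under 4.4.3, for a probably or definitely related event of moderate or severe intensity, "the intervention will be discontinued for that participant and standard care will be provided"; leaving the study is not stated, and follow-up assessments could continue.
- The sentence in 4.14 is reasonable for women who exit by completing Week 16. The difficulty is that it applies equally to those who exit early.

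The add-on arm alone carries oil-related risks (4.4.3, 8.2), so unequal loss between arms is possible. Both arms carry the distress risk of CBT-I (8.2), and no rates are given, so a direction of bias cannot be asserted.

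The full protocol may hold more detailed safety procedures. That does not dispose of the point, because the article states these rules outright and they conflict as stated.

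**Conclusion.** The point holds in a limited form. Safety data collection ends at withdrawal, including withdrawal for a serious adverse event or an emergent psychiatric condition. The one route for later events depends on a prior relatedness judgement and has no planned contact behind it. The later course of open events and new events up to Week 16 are therefore incompletely and selectively captured, contrary to 4.4 and to the resolution-date field in 4.4.2 and 4.14.

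The event count up to exit is intact unless a woman asks for removal of her data. The exposure is about 9 women at the planned attrition; how many would leave because of harm is unknown, and the percentage illustrations rest on assumed counts. The conclusion assumes that 4.8.4 applies to every withdrawal, as its wording implies. The sections should be reconciled, but the gap does not undermine the trial.

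**What to change.** Reconcile 3.8, 4.8.4 and 4.14 on data collection, leaving clinical management as it stands.

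- For women who have not refused contact, follow adverse events open at withdrawal, for data purposes, to resolution or stabilisation.
- For the same women, record all adverse events to Week 16 regardless of suspected relatedness, using the telephone check-ins (3.9.3) and telehealth visits (4.8.1) already planned. Assess relatedness after recording.
- Confine the post-exit rule in 4.14 to events after Week 16 or after a woman has refused contact.
- Report by arm the number of withdrawals for adverse events and the number of records removed on request.

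Whether coded adverse event records should be exempt from removal is an ethics and consent question to settle with the ethics committee; the fix does not depend on it.

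The cost is amended wording in the protocol and consent form, submitted for ethics approval, and a few calls to at most about 9 women at planned attrition.
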